#### Tertiary outcome

2.10.3

**The Canadian Occupational Performance Measure (COPM)** assesses perceived performance in activities of daily living, functional mobility, life participation, and occupational performance. Through a semi-structured interview, participants identify activities they want to, need to, or are expected to perform. Participants establish one long-term goal and rate their performance and satisfaction towards the set goal on a numeric ranking scale from zero to ten. A caregiver or proxy may respond on behalf of the participant.

#### Exploratory outcomes

2.10.4

Three days (72 h) of movement behavior will be assessed with IMUs and analyzed using a deep-learning neural network [20]. We will describe the overall change in movement behavior patterns after the intervention, including changes in the time spent walking, standing, sitting, and lying down and the number of transitions between these states. We will also examine relative extremity usage.

### Other trial data

2.11

**Adverse events** during the intervention period (T1-T2) will include both serious (e.g. death, hospitalization) and non-serious adverse events (e.g. pain, fatigue) [24]. Harms will be evaluated using relative risk between the Music Motion Feedback and control groups for both event types.

**Demographic data**, collected during baseline assessment through self- or proxy reports for all participants, will include age, sex, daytime and nighttime occurrence of pain, living arrangements, occupation status, and leisure time activities.

**Clinical information** such as GMFCS-E&R classification, type of CP, and affected body parts will be examined on-site during baseline assessment.

**Routine BoNT-A injections** (date and muscles) will be recorded based on participant or caregiver reports at the virtual conference and verified in medical records.

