### Eligibility criteria

2.3

Individuals with CP aged 15 to 25 at enrollment are eligible to participate if they have sensorimotor deficits in at least one limb and are classified within GMFCS-E&R levels I-V. They must show motivation to develop new motor skills or recover lost ones, as indicated by their or their proxy's ability to express a specific goal they wish to achieve. They must be able to follow instructions independently or with caregiver support and be capable of providing informed consent to participate. Individuals will be excluded from participation if they have dyskinetic CP, significant health risks, have undergone major orthopedic or neurosurgical procedures within six months preceding enrollment or planned during the intervention period, or minor procedures that could temporarily affect training or movement behavior within one month before enrollment or during the trial. Eligibility for borderline cases is determined by the principal investigator in consultation with the treating physician. Botulinum neurotoxin type A (BoNT-A)-naïve individuals will be excluded if they have received intramuscular injections within three months before baseline. Individuals undergoing routine BoNT-A injections are eligible, and injections in muscles not directly targeted by the training program do not preclude participation.

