### Randomization

2.6

Participants will be assigned to groups using matched pairs randomization with a 1:1 allocation ratio. Matching will be based on dichotomized ages (adolescents 15–19 years, young adults 20–25 years) and GMFCS-E&R classifications. Within each stratum, participants will be grouped into pairs. A computer-generated randomization sequence will assign the first participant in each pair to either group, with the second assigned to the alternate. [name] will enroll participants and extract age and GMFCS-E&R classifications to create pairs. A third-party allocator will conduct randomization to ensure allocation concealment, with the sequence securely stored and revealed only after statistical analysis is complete.

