### Statistical analysis

2.13

A statistical analysis plan will be developed in collaboration with a biostatistician and uploaded to ClinicalTrials.gov before the last participant's first visit.

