#### Sample size

2.13.2

The sample size calculation is based on a systematic review and meta-analysis of controlled trials assessing extrinsic feedback on recovery and motor learning in individuals with brain injuries. The analysis found a significant Standardized Mean Difference of 0.76 with participants in identical motor training programs, differing only in feedback provision [16]. With 58 participants, we will attain a statistical power of 81.8 %. To account for potential dropouts, we plan to enroll 70 participants (35 in each group).

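### Relative risk is the only measure named for serious harms, and with 35 per arm it has no finite value if the control arm has no event

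*Protocol article*

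**What the plan says.** Section 2.11 (Other trial data) of the protocol article collects adverse events over the intervention period, T1 to T2, which is 12 weeks. It divides them into serious events, with death and hospitalization as examples, and non-serious events, with pain and fatigue as examples. It then sets the measure: "Harms will be evaluated using relative risk between the Music Motion Feedback and control groups for both event types". The article names no risk difference, exact method, zero-cell rule or descriptive-only option.

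Section 2.13.2 plans 70 participants, 35 per group, and section 2.6 uses "matched pairs randomization with a 1:1 allocation ratio". Section 2.3 admits people who "are classified within GMFCS-E&R levels I-V" and excludes those with significant health risks or with recent or planned major orthopedic or neurosurgical procedures. The Discussion projects 70% of participants at levels I-II. No section gives an expected adverse event rate.

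Section 2.13 leaves further detail to a later document: "A statistical analysis plan will be developed in collaboration with a biostatistician".

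**The concern.** Relative risk divides by the control-arm risk. For pain or fatigue, which should occur in both arms, this is a reasonable choice. Death and hospitalization over 12 weeks of home training are likely to be sparse, and 35 controls may include no case. The ratio is then x/0 or 0/0. If either arm is empty, the ordinary log-based interval does not exist either.

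The harm summary for the most important events could then have no finite value, or could depend on a continuity constant that the article does not set. If neither arm has a serious event, relative risk says nothing, although 35 per arm without an event still limits how large an excess could be.

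**Working it through.** **Inputs.** 35 per arm (section 2.13.2); a 12-week window and relative risk for both event types (section 2.11); 1:1 allocation (section 2.6). The serious-event risk *p* per participant is assumed, because the article gives none.

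**The plan's own figure.** The harms sentence contains no number. The sample size behind the 35 per arm does reproduce. With 29 per arm, a standardized difference of 0.76 and two-sided alpha 0.05 (inferred from the 95% interval), power is 82.5% by the normal formula and 81.2% by the t-test, against the stated 81.8%. Going from 58 to 70 participants allows for 1 - 58/70 = 17% dropout.

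**How often an arm is empty.** Take equal risk in both arms, independent participants and *q* = (1 - *p*)^35. Then P(control arm empty) = *q*, P(at least one arm empty) = 1 - (1 - *q*)^2 and P(both empty) = *q*^2.

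| Assumed risk *p* | Control empty: no finite relative risk | At least one empty: no log-based interval | Both empty: 0/0 |
|---|---|---|---|
| 1% | 70% | 91% | 49% |
| 2% | 49% | 74% | 24% |
| 3% | 34% | 57% | 12% |
| 5% | 17% | 30% | 2.8% |
| 10% | 2.5% | 4.9% | under 0.1% |

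The control arm is empty in half of trials at *p* = 1 - 0.5^(1/35) = 1.96%. With 29 per arm the control arm is empty in 75%, 56% and 23% of trials at 1%, 2% and 5%. At *p* = 20%, as might apply to a common non-serious event, the figure with 35 per arm is about 0.04%.

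**What relative risk gives when the control arm is empty.** The score interval solves (p1 - θ·p2)^2 / V(θ) = 1.96^2, where p1 and p2 are the observed risks and V(θ) is the variance under the constraint that the true ratio is θ. With no control event only the lower limit is finite:

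- 1 v 0: 0.27 to infinity
- 2 v 0: 0.54 to infinity
- 3 v 0: 0.82 to infinity

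A continuity correction adds *k* to each cell. At 3 v 0 the ratio becomes (3 + *k*)/*k*, with log standard error sqrt[1/(3 + *k*) + 1/*k* - 2/(35 + 2*k*)].

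- *k* = 0.5: ratio 3.5/0.5 = 7.0; standard error sqrt(1/3.5 + 1/0.5 - 2/36) = 1.49; 95% CI 0.37 to 131.
- *k* = 1: ratio 4/1 = 4.0; standard error sqrt(1/4 + 1/1 - 2/37) = 1.09; 95% CI 0.47 to 34.

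The same data give 7.0 or 4.0 depending on the constant.

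**What the risk difference gives.** The Newcombe interval combines the Wilson limits (l, u) of each arm. Its lower limit is d - sqrt[(p1 - l1)^2 + (u2 - p2)^2] and its upper limit is d + sqrt[(u1 - p1)^2 + (p2 - l2)^2]. For 0/35 the Wilson upper limit is 1.96^2/(35 + 1.96^2) = 3.84/38.84 = 9.9%.

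| Events, feedback v control | Risk difference, points (95% CI) | Relative risk |
|---|---|---|
| 0 v 0 | 0.0 (-9.9 to 9.9) | 0/0 |
| 1 v 0 | 2.9 (-7.3 to 14.5) | no finite value |
| 2 v 0 | 5.7 (-5.0 to 18.6) | no finite value |
| 3 v 0 | 8.6 (-2.8 to 22.4) | no finite value |

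The risk difference has a finite estimate and finite limits in every row.

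**The case against.** The strongest reply is that this is detail for the SAP. Zero-cell rules, interval methods and companion measures are what a condensed protocol article leaves out, and section 2.13 promises a SAP written with a biostatistician. Relative risk is a conventional harm measure, the sentence does not exclude others, and no test, stopping rule or powered safety claim depends on it. That is right as far as it goes. What remains is that section 2.11 is not silent: it chooses a measure and applies it expressly to serious events, where it is most likely to fail.

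The practical loss is also small. Event counts and denominators are needed to form a relative risk, and once they are reported any reader can derive the risk difference. A score interval for the ratio exists when only the control arm is empty, and at 3 v 0 both measures leave no effect within the interval. At 0 v 0 the risk-difference interval of ±9.9 points is too wide to reassure about death or hospitalization. All of this stands and keeps the point minor. Imprecision, however, is not the complaint; the absence of a finite value is.

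The frequency of the problem rests wholly on assumed risks. That also stands. The exclusions in section 2.3 and the projected 70% at levels I-II favor the lower part of the range. A risk near 10% cannot be ruled out while levels I-V are eligible, and there the problem is rare.

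Finally, showing relative risk only when both arms have events makes part of the report depend on the data. This has little force if the risk difference is the fixed main measure whatever the counts.

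**Conclusion.** The point holds, at low severity. That relative risk has no finite value with an empty control arm, and that a risk difference always has one, is arithmetic and needs no assumed rate. How often it would matter does depend on assumption. With 35 per arm, a common 12-week serious-event risk and independent participants, the control arm is empty in 34% to 70% of trials at risks of 3% down to 1%, in 17% at 5% and in 2.5% at 10%.

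The criticism applies to serious events only; relative risk is suitable for common non-serious ones. The blinded statistician (section 2.7) and the planned SAP limit the risk of a choice driven by the data, and the SAP may already deal with the matter.

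**What to change.** Add one sentence to section 2.11 or to the SAP. Suggested wording: *For serious adverse events, the number of participants with at least one event will be reported by arm, and the main measure will be the risk difference with a Newcombe or exact 95% confidence interval; relative risk will be given in addition only when both arms have events. For non-serious adverse events, relative risk will be reported.*

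This uses data already collected. The downside is that the absolute interval for serious events will be wide, and no choice of measure removes the imprecision that comes with 35 per arm.

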### Data management

2.12

All data collection and handling will comply with data protection regulations to ensure participant confidentiality and privacy. Clinical assessments will be recorded on paper and uploaded for storage in a RedCap database.

### Statistical analysis

2.13

A statistical analysis plan will be developed in collaboration with a biostatistician and uploaded to ClinicalTrials.gov before the last participant's first visit.

#### Superiority margin

2.13.1

The change in real-world daytime extremity movement over 72 h from baseline to follow-up (T2) and long-term follow-up (T3) determines the superiority margin, set at a 10 % increase for both upper and lower extremities.

Due to the wide variability in extremity movement among adolescents and young adults with CP at GMFCS-E&R levels I-V (upper: 5.6 %–54.4 %; lower: 1.3 % - 19.4 % of daytime) ([name], manuscript), percentage change was chosen over absolute change. Superiority is claimed if the lower bound of the 95 % confidence interval for the Music Motion Feedback group surpasses the 10 % margin. While no universal threshold for clinically meaningful improvement exists, this margin aligns with chronic stroke findings, where a change of 575–752 accelerometer counts is considered a meaningful improvement (15 %-20 %) [25].

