### Trial design

2.1

This is a two-arm parallel assignment randomized clinical superiority trial in which adolescents and young adults with CP self-administer home-based motor training with or without Music Motion Feedback. Outcomes will be assessed before randomization, after 12 weeks of intervention (end of intervention - T2), and to evaluate the sustainability of potential improvements after 24 weeks (follow-up - T3). The trial design is visually presented in Fig. 1.

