### Outcomes

2.10

Baseline (T1) and outcome assessments (T2, T3) will be performed on weekdays within a week before intervention commencement (T1), within a week after the end of intervention (T2), and 24 weeks after intervention initiation (T3). Assessments will be conducted at approximately the same time of day for each participant to minimize intraday variability. The primary endpoint is T2. Please view the assessment timeline in Fig. 2.

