**Fig. 2 fig2:**
[figure not shown]
SPIRIT figure. Schedule of enrollment, interventions, and assessments. **Note:***t*_1_ baseline, *t*_2_ 12 weeks (primary endpoint), *t*_3_ 24 weeks, *t*_4_ 26 weeks. Gross Motor Functional Classification Scale-Expanded and Revised (GMFCS-E&R), Action Research Arm Test (ARAT), Gross Motor Function Measure-66 (GMFM-66), 6-min walk test (6MWT), Canadian Occupational Performance Measure (COPM). (a) Systematic inquiry of potential events during virtual conferences. (b) Data will be collected continuously through the TIA app. (c) Only the Music Motion feedback group can be tracked for staying at or above the intensity threshold. (d) Involves completing the participant's involvement in the trial, including final data review, administrative tasks, and confirming that all study procedures have been appropriately completed.

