##### The primary outcome

2.13.3.1

A linear mixed-effects model (LMM) will analyze the percentage change in real-world targeted extremity movement from baseline (T1) to 12 weeks (T2) and 24 weeks (T3). The model will include fixed effects for Group (Music Motion Feedback vs. Control), Time (T1-T2, T1-T3), and their interaction (Group × Time), adjusted for baseline extremity movement time and sex. A random intercept for each participant will account for individual differences in baseline differences, and a random slope for Time will model variability in improvement rates. If residuals indicate non-normality, a logarithmic transformation will be performed.

Given the moderate sample size, the analysis will be conducted using restricted maximum likelihood estimation. A Holm-Bonferroni correction will be applied to adjust for multiple comparisons. A planned subgroup analysis will evaluate age group effects (adolescents vs. young adults).

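### T2 is the declared primary endpoint, but the superiority section brings in T3, and no passage names the contrast that decides the primary outcome

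*Protocol article*

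**What the plan says.** The time point is declared in section 2.10 (Outcomes): "The primary endpoint is T2". The note to Fig. 2 repeats it: "12 weeks (primary endpoint". Section 2.1 (Trial design) gives the later visit a different purpose: "to evaluate the sustainability of potential improvements after 24 weeks (follow-up - T3".

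Section 2.13.1 (Superiority margin) is the only place with a success rule. It opens with "The change in real-world daytime extremity movement over 72 h from baseline to follow-up (T2) and long-term follow-up (T3) determines the superiority margin" and sets the margin at a 10 % increase. The rule itself reads: "Superiority is claimed if the lower bound of the 95 % confidence interval for the Music Motion Feedback group surpasses the 10 % margin". That sentence names neither a time point nor a between-group difference.

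Section 2.13.3.1 (The primary outcome) says the mixed model "will analyze the percentage change in real-world targeted extremity movement from baseline (T1) to 12 weeks (T2) and 24 weeks (T3"). On its terms: "The model will include fixed effects for Group (Music Motion Feedback vs. Control), Time (T1-T2, T1-T3), and their interaction (Group × Time"), with adjustment for baseline movement time and sex. A Holm-Bonferroni correction follows, without saying which comparisons it covers. No term or contrast is identified as the primary result.

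**The concern.** Three places point to T2 as the time of the primary comparison. The section that says when superiority may be claimed attaches its margin to T2 and T3 together. A reader who takes that sentence at face value may think that both times must pass.

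The difference matters because training ends at week 12, so a benefit that is present at T2 and weaker at T3 is a plausible result. Such a trial succeeds on the declared endpoint and may fail under a joint rule.

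The model section does not settle the matter. In a model of raw scores that includes a baseline level, the Group × Time term carries the treatment effect. Here the response is already change from baseline, so the same label means something else. Someone used to the raw-score layout could read the wrong line of the output.

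**Working it through.** **Inputs.** SMD 0.76, 58 analysed and power 81.8% come from section 2.13.2; 58 at 1:1 allocation (section 2.6) is 29 per arm. The two-sided 5% level is inferred from the 95% confidence interval in section 2.13.1. The correlation between the T2 and T3 estimates is not in the document and is an assumption, shown over a range. All tests below are of zero difference, not of the 10% margin.

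**1. The plan's own figure.** For one comparison at one time, the expected z is 0.76 × √(29/2) = 2.894.
- Normal approximation: power = Φ(2.894 − 1.960) = 82.5%.
- Noncentral t with 56 degrees of freedom: 81.2%.

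The stated 81.8% lies between the two. A one-sided 5% test would give 88.8% and does not match. The sample size therefore fits a single between-group comparison at a single time.

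**2. Both times required, effect fully sustained (0.76 at T2 and T3).** Power = P(Z2 > 1.96 and Z3 > 1.96), with both means 2.894 and correlation r.

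| r | Power, both required |
|---|---|
| 0 | 68.0% |
| 0.3 | 70.3% |
| 0.5 | 72.2% |
| 0.7 | 74.5% |
| 0.9 | 77.9% |

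**3. Effect halved at T3 (0.38).** The expected z at T3 is 0.38 × √(29/2) = 1.447. T2 alone still succeeds in 82.5% of trials and T3 alone in 30.4%. Both succeed in 27.6% (r = 0.3), 29.0% (r = 0.5) and 30.0% (r = 0.7). At r = 0.5, the two times give different answers in 82.5 + 30.4 − 2 × 29.0 = 54.9% of trials.

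**4. What Group × Time estimates.** Let D2 and D3 be the group differences in percentage change at T2 and T3. Time has only the levels T1-T2 and T1-T3, so Group × Time = D3 − D2. In a REML simulation (29 per arm, 400 runs, assumed correlation 0.6, random intercept, no covariates):

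| True effect T2 / T3 | Mean interaction | Significant |
|---|---|---|
| 0.76 / 0.76 | −0.01 | 5.8% |
| 0.76 / 0.38 | −0.38 | 35% |
| 0.76 / 0 | −0.77 | 90% |

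A full and lasting benefit leaves the interaction at its nominal level. In these three settings, with T1-T2 as reference level, the Group coefficient recovers the T2 difference (mean 0.75 to 0.79, significant in 84% to 86% of runs). The model can therefore supply the required estimate.

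**5. The unnamed Holm family.** If T2 and T3 formed the family, the smaller p-value would be tested at 0.025. Power of one comparison at that level is 72.2% (t) or 74.3% (normal), which is what T2 has unless T3 is rejected first. Whether the primary test is inside the family therefore matters for power.

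**The case against.** The strongest reply is that the time point is already settled. T2 is declared twice, T3 has its own stated purpose, and the sentence in section 2.13.1 can be read as saying only which changes the margin refers to. Since the claim sentence is silent on time, the declared endpoint is its natural reading. This largely stands, and it limits the severity. It does not remove the conflict, because the sentence stands in the section that defines superiority and directly precedes a rule with no time point.

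A second reply is that a journal article may leave the exact contrast to the statistical analysis plan, which section 2.13 promises. That holds for silence about coding or contrasts. It does not cover a disagreement between sections 2.10 and 2.13.1 of the same article.

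Three stronger readings are tempting and not supported:
- **That T3 alone, either time, or an average could decide the trial.** No passage proposes any of these.
- **That the false-positive rate is about 9%.** Accepting either time uncorrected would give 9.1% at r = 0.5 (7.8% to 9.8% for r = 0.8 to 0). The protocol states a Holm-Bonferroni correction, and if T2 and T3 were its family the rate would be about 4.0% to 4.9% over the same range.
- **That the trial will be judged on the interaction.** Section 2.13.3.1 lists it as a model term and never calls it the deciding test.

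Nor do the documents show that the choice will be made with results in view: the statistician is blinded (section 2.7) and the analysis plan is due before the last participant's first visit.

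**Conclusion.** The point holds as an inconsistency that should be fixed, not as one that undermines the trial. T2 is the declared endpoint and the stated power fits it. The superiority section adds T3, its claim sentence gives no time and is worded for one group, and the model section names neither the deciding contrast nor the Holm family.

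On a both-times reading, power would be about 70% to 75% instead of 81.8% even with a lasting effect. With a half-sized effect at T3, success would fall from 82.5% to about 28% to 30%. These figures rest on an assumed correlation of 0.3 to 0.7, an assumed T3 effect and tests of zero difference. They show how far the readings diverge. They do not estimate this trial's chance of success under a 10% margin.

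**What to change.** In sections 2.13.1 and 2.13.3.1, and in the analysis plan:

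1. State that the sole primary contrast is the adjusted between-group difference in percentage change at T2, with its 95% confidence interval, estimated from the mixed model at the T1-T2 level.
2. Word the superiority rule for that between-group contrast, replacing the interval for the Music Motion Feedback group alone, and say how the 10% margin applies to it.
3. Remove T3 from the superiority rule and report the T3 difference as a secondary estimate of sustainability.
4. State that Group × Time is descriptive: it shows how the group difference changes from T2 to T3.
5. Name the Holm-Bonferroni family and state that the single primary T2 test is outside it.

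The cost is wording, with no added data or participants. T3 gives up any claim to the primary decision, in line with the purpose that section 2.1 gives it. The change should be made and declared before group results are known.

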### Objectives

1.1

The THRIVE-CP trial evaluates the effectiveness of incorporating Music Motion Feedback into home-based motor training for adolescents and young adults with CP compared to home-based motor training without Music Motion Feedback. We hypothesize that the Music Motion Feedback group will demonstrate greater improvements in real-world movement behavior, functional improvement, limb function, and perceived goal performance than the control group. Additionally, we expect the Music Motion Feedback group to attend and adhere more to the training program.

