#### Primary outcome

2.10.1

The primary outcome is the percentage change in real-world daytime movement of the targeted extremity (right or left arm or leg). We hypothesize this reflects the impact of the anticipated increase in capacity from motor training programs on real-world movement behaviors. Data will be collected from seven IMUs worn by participants for 72 consecutive hours and analyzed using a deep-learning neural network. The methodology details have been previously described [20]. IMUs will be attached with adhesive patches on the sternum, wrists, thighs, and lower legs to collect 3-axis accelerometer and gyroscope data. A custom neural network converts the signals into images and processes them through several convolutional layers, extracting features to recognize movement behaviors. Movement behaviors beyond limb movement will be utilized for exploratory outcomes. Daytime will be recorded in participant logs, noting the times in bed, lights out, devices off, wakefulness, and when they leave bed.

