## Discussion

3

Music Motion Feedback is a promising approach to improving movement behavior and functional improvement in adolescents and young adults with CP, potentially increasing activity and reducing disability. By providing real-time extrinsic feedback in tailored home-based training, we utilize established motor learning principles to enhance adherence and long-term outcomes. However, the THRIVE-CP trial faces generalizability limitations, such as recruiting intrinsically motivated participants and the bias of CP severity affecting participation, with 70 % of participants projected at GMFCS-E&R I-II. Additionally, those with lower technological literacy may struggle with adherence to the Music Motion Feedback. The trial lacks a usual care group due to recruitment constraints, limiting our ability to assess the separate effect of Music Motion Feedback. However, the TRIVE-CP trial addresses a critical challenge faced by adolescents and young adults with CP. If effective, this technology could provide an accessible and scalable method to enhance adherence to home-based motor training and foster meaningful progress in real-world movement behavior and functional abilities. The findings may significantly impact practice by promoting sustainable behavioral changes and improving the quality of life for individuals with CP.

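### The stated rule claims superiority from the feedback arm's own change from baseline, so superiority can be declared when feedback adds nothing over control

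*Protocol article*

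**What the plan says.** Section 2.13.1 (Superiority margin) sets the margin on the change in daytime extremity movement "from baseline to follow-up (T2) and long-term follow-up (T3) determines the superiority margin, set at a" 10% "increase for both upper and lower extremities". It continues: "Superiority is claimed if the lower bound of the" 95% "confidence interval for the Music Motion Feedback group surpasses the" 10% margin. The section does not mention the control arm, and nowhere else does the article say when superiority is claimed.

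The rest of the article is comparative:

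- Section 2.1 describes a "two-arm parallel assignment randomized clinical superiority trial".
- Section 1.1 evaluates feedback training "compared to home-based motor training without Music Motion Feedback".
- Section 2.13.2 bases the sample size on a standardized mean difference (SMD) of 0.76 between arms that differ only in feedback.
- Section 2.13.3.1 fits Group, Time and Group × Time.

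Section 2.10.1 says the primary outcome should reflect "the anticipated increase in capacity from motor training programs on real-world movement behaviors", and section 2.4 gives that training to both arms. The Discussion says the lack of a usual-care group has the effect of "limiting our ability to assess the separate effect of Music Motion Feedback".

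**The concern.** The quantity (change from baseline), the group (feedback arm) and the threshold (a fixed 10%) are all single-arm. A rule built from them asks whether participants who train with feedback improve by more than 10%. It does not ask whether they improve more than participants who train without it.

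Because the training is common to both arms, its effect and any practice effect enter the feedback arm's mean in full. The trial could therefore report superiority with identical results in the two arms. It could also fail to report superiority when feedback clearly beats control but the feedback arm's own change is not clearly above 10%.

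The Discussion shows a related confusion. A training-only control is exactly what isolates the effect of feedback. What the missing usual-care arm prevents is measuring the effect of the training programme.

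**Working it through.** **Inputs from the article.** Margin 10% and 95% interval (2.13.1); SMD 0.76, 58 evaluable participants, power 81.8% (2.13.2); 1:1 allocation (2.6), hence 29 per arm. **Assumed, because not given:** SD of percentage change 15 to 50 points; true mean gain g shared by both arms; normal data; two-sided alpha of 0.05, inferred from the 95% interval.

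**Step 1: what the stated power refers to.** For a two-sample t test against zero, the noncentrality is 0.76 × √(29/2) = 2.894. With 56 degrees of freedom and critical value 2.003, power is 81.2%; the normal approximation gives 82.5%. Both are close to the stated 81.8%. A one-sided test (88.8%) and a paired test on 29 pairs (97.7%) do not fit. The trial was therefore sized for a between-arm difference tested against zero.

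**Step 2: the written rule when feedback adds nothing.** The rule is met when the lower 95% limit of one arm's mean exceeds 10. Its probability is

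P = 1 − F(t₀.₉₇₅,₂₈; df = 28, ncp), with ncp = (g − 10)/SD × √29,

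where F is the noncentral t distribution function. Example: for g = 20 and SD = 30, ncp = (10/30) × 5.385 = 1.795, the critical value is 2.048, and P = 41%.

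| Shared true gain | SD 15 | SD 20 | SD 30 | SD 40 | SD 50 |
|---|---|---|---|---|---|
| 5% | <0.1% | 0.1% | 0.2% | 0.5% | 0.7% |
| 10% | 2.5% | 2.5% | 2.5% | 2.5% | 2.5% |
| 15% | 41% | 25% | 14% | 10% | 7% |
| 20% | 93% | 74% | 41% | 26% | 18% |
| 25% | 99.9% | 97% | 74% | 50% | 34% |
| 30% | 100% | 99.9% | 93% | 74% | 55% |

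A simulation at g = 20, SD = 20 also gave 74%. With all 35 per arm and g = 20, the figures for SD 15, 20, 30 and 40 are 97%, 82%, 48% and 30%. A between-group test against zero errs in this direction 2.5% of the time in every cell.

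**Step 3: the opposite failure.** Suppose control does not change and feedback has exactly the planned effect, so the feedback arm's mean gain is 0.76 × SD. The written rule then succeeds in 7%, 27% and 60% of trials for SD 15, 20 and 30. The between-group test succeeds in 81%.

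**Step 4: the margin moved to the between-arm difference.** If the lower limit of the difference must exceed 10 points, the standardized distance at the planned effect is (0.76 × SD − 10)/SD.

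| SD | True difference | Power, 29 per arm | Per arm for 80% power |
|---|---|---|---|
| 15 | 11.4 | 5% | 1803 |
| 20 | 15.2 | 16% | 233 |
| 30 | 22.8 | 36% | 87 |
| 40 | 30.4 | 48% | 61 |

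False claims under no difference are then below 0.2%, but the stated power is lost.

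**The case against.** The best defence is that the sentence is loose shorthand for the Group × Time contrast. It stands under a superiority heading in a two-arm trial with a comparative hypothesis, a comparative model and a comparative power calculation. The model in 2.13.3.1 would still estimate the between-group effect, so the randomised comparison survives in the analysis even though the decision sentence bypasses it. That much is fair: two incompatible criteria coexist.

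The defence does not rescue the sentence. Nothing in the article ties the superiority claim to that contrast, and the margin is expressly set on change from baseline. If the 10% was meant for the between-group difference, step 4 shows that it conflicts with the stated power. The wording has to change on either reading. Leaving details to the later analysis plan does not help, because this is a rule stated wrongly and not a rule left out.

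Two limits on the size do stand. The false-claim rate exceeds 2.5% only if the shared gain exceeds 10%, and the article expects a gain without giving its size. Regression to the mean should not be counted among the causes, since section 2.3 does not select on low baseline movement.

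**Conclusion.** Wrong as written. The only stated criterion for superiority is single-arm and contradicts the objective, design, sample size and primary model.

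The false-claim rate depends on how much training alone lifts both arms. It is at or below 2.5% for shared gains up to 10%. For a shared gain of 20%, it runs from 18% (SD 50) to 93% (SD 15). The chronic-stroke benchmark cited in 2.13.1 is 15% to 20%, so gains above 10% are within the range the protocol itself calls meaningful. All these rates rest on assumed SDs and gains and on 29 per arm. The contradiction does not depend on those assumptions.

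This must be fixed before results are read, because the criterion decides the trial's headline conclusion.

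**What to change.** Replace the decision sentence in 2.13.1 with: *Superiority is claimed if the two-sided 95% confidence interval for the between-group difference (Music Motion Feedback minus control) at T2, from the primary model, lies entirely above zero.* Keep 10% only as a benchmark for discussing the clinical relevance of the estimated difference.

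This version agrees with T2 as the primary endpoint (2.10) and with the stated 81.8% power. If the sponsor does intend a 10-point margin on the between-group difference, that must be stated and the sample size recalculated; on the assumed SDs of 15 to 40 points it would need about 61 to 1803 per arm.

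Correct the Discussion to say that, without usual care, the effect of the training programme itself cannot be assessed, while the effect of feedback can.

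With the zero null, the cost is an edit to the protocol and analysis plan and a registry update. No added participants or data are needed.
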